### Clinical management

Members of the clinical team and study team will all receive pre- and peri-trial training on the management of severe malaria and the use of BCV. A manual of operations for the trial will be available for the study team, to anticipate and troubleshoot any potential issues. This is the approach that was taken for training of AirVo2 in the COAST trial and this ensured adherence to the protocol
^
46
^. Our programme has a dedicated high dependency ward with a long track record of research and care for children with cerebral malaria and has the relevant expertise in the management of this condition. The usual protocol for management of seizures will be followed.

One potential risk of BCV use is aspiration; however this risk is minimal (<1%)
^
35
^, and further all children with coma routinely have nasogastric tubes placed (to drain gastric contents and secretions) and regular suction (oropharynx) which would apply to all children enrolled in this study as this is part of usual practice. The other potential risk is retention of carbon dioxide, which will be explored in detail in this Phase I study, using non-invasive end-tidal capnography (E’CO2) monitoring. High measures of E’CO2 will be verified by venous blood gas measurement (PCO2). If indicated (PCO
_2_ >45 mmHg) then AIRVO2 will be started to wash out CO
_2_ since hypercarbia can worse brain swelling. Continuous capnography is increasingly being used across Africa and supported by the Safe Surgery initiative
^
48
^, as it provides information on the efficiency of respiratory cycle (in non-intubated as well as intubated patients) which is an important parameter to capture in children with cerebral malaria as well as providing a continuous reading of expired CO2. As transcutaneous monitoring is not possible (or affordable in the long-term) our group (and external expert collaborators) prefer use of capnography by regular sampling expired gas from nasal cannulae. All abnormal measurements will be checked against a venous blood gases (0.2mls blood) as an alternative method of measurement. Finally, bag and mask ventilation is also available for children developing short term apnoea who are not ‘rescued’ by BCV.

Children will initially receive parenteral antimalarial treatment (artesunate), followed by an oral course of artemisinin combination therapy, on day 3 (or when the child can safely take and retain oral feeds and fluids). All trial patients will receive intravenous antibiotics. Intravenous maintenance fluids will be given at a rate of 4ml/kg/hour until the child is able to drink and retain oral fluids. Antipyretics and treatment for hypoglycaemia and other treatments will be given as clinically required and will be administered according to nationally agreed protocols. Children with Hb <4g/dl (or Hb <6 g/dl and respiratory distress) will be transfused with 20mls/kg of whole blood.

### Trial withdrawal

In consenting to the trial, patients are consenting to trial treatment (BCV with or without prophylactic anti-convulsants), data collection and follow-up. If a carer wishes to withdraw their child from trial treatment, the investigator will explain the importance and benefits of follow-up, and the value of allowing routine clinical data to be used for trial purposes. Patients/parents are free to discontinue any part of their trial treatment or discontinue from follow up. After the participant has entered the trial the clinician remains free to give alternative treatment to that specified in the protocol at any stage if he/she feels it is in the participant’s best interest, but the reasons for doing so should be recorded. In these cases, the participants remain within the study for the purposes of follow-up and data analysis. All carers and participants are free to withdraw at any time from the protocol treatment without giving reasons and without prejudicing further treatment. If they do not wish to remain on trial follow-up, however, their decision must be respected and the patient will be withdrawn from the trial completely.

### Protocol treatment discontinuation

An individual patient may stop treatment early or be stopped early for any of the following reasons:

▪   Unacceptable toxicity or adverse event

▪   Intercurrent illness that prevents further treatment

▪   Any change in the patient’s condition that justifies the discontinuation of treatment in the clinician’s opinion

▪   Withdrawal of consent for treatment by the patient or parent.

Participation in the trial is entirely voluntary, and parents, carers or older children may choose to discontinue the trial treatment at any time without penalty or loss of benefits to which they are otherwise entitled. Although not required to give a reason for discontinuing their trial treatment, a reasonable effort should be made to establish this reason while fully respecting the patient's rights.

Patients should remain in the trial for the purpose of follow-up wherever possible (unless the patient withdraws their consent for follow-up). If a patient withdraws from the trial, the medical data collected during their previous consented participation in the trial will be kept and used in analysis. This will also apply to parents/carers who withdraw from the trial after assent, that have not completed the deferred consent process. Consent for future use of stored samples already collected can be refused when leaving the trial early (but this should be discouraged and should follow a discussion). If consent for future use of stored samples already collected is refused, then all such samples will be destroyed following the policies of the institution.

### Trial monitoring

The trial will be monitored by the Clinical Trial Facility in Kilifi which oversees standards and quality of all trials conducted through the KWTP and through its monitoring systems and standard operating procedures are organised to ensure that all sites can be monitored with equal independence and rigor. All monitors will be appropriately qualified and trained. At each monitoring visit the monitors will:

▪   verify completeness of Trial Master File

▪   confirm adherence to protocol

▪   review eligibility verification and consent procedures

▪   look for missed clinical event reporting

▪   verify completeness, consistency and accuracy of data being entered on case report forms (CRF)s

▪   evaluate drug accountability

▪   provide additional training as needed

The monitors will require access to all patient medical records including, but not limited to, laboratory test results and prescriptions. The investigator (or delegated deputy) should work with the monitor to ensure that any problems detected are resolved.

### Data management

All clinical and laboratory data will be recorded in the CRF and stored with a unique serial number identifier. Data will be entered onto OpenClinica. All data will be regularly backed up and backup copies stored both on and off site. Paper records will be archived in locked cabinets. These cabinets will have limited access with prior authorisation. All data will be partially- anonymized prior to presentation or publication of any results. Archive documents will be sent for long term storage (10 years) at an appropriate facility according to national policies.

### Confidentiality

Participant’s identification data will be required for the registration process. All clinical and laboratory data will be recorded in the CRF and stored with a unique serial number identifier. Information will only be made available to those caring for the child and those directly involved with the study. Data will be entered onto OpenClinica (FDA approved, web-based application). All data will be regularly backed up and backup copies stored both on and off site. Paper records will be archived in locked cabinets. These cabinets will have limited access with prior authorisation. All data will be partially- anonymized prior to presentation or publication of any results. All clinical data will be held confidentially, and personal identifiers will be removed before analysis of the data and presentation of the results.

### Data sharing

After completion of the study, requests for data access from researchers outside the study team will be considered by a subgroup of the Centre Scientific Committee (Data Governance Committee), and where indicated, requestors will be asked to develop scientific protocols for approval of secondary analyses. The potential to share data will be included in the participant Information and Consent Form.

### Statistical analysis

Clinical data will be summarised using means and medians were appropriate for continuous data depending on the distribution. Analyses will follow intention-to-treat. Primary and secondary endpoints will be described using means or medians or proportions. For the primary endpoint (cumulative time with epileptogenic seizure activity over 36 hours), children who die without recovering from coma will be imputed to have a cumulative time of 36 hours (maximum expected coma duration). As this is a Phase I trial no subgroup analyses are planned.

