### Interim reviews

The Data Monitoring Committee (DMC) will review data from the first 10 children enrolled to receive LVT. If the DMC consider that it reduces seizures that are short lived and not clinically-relevant i.e. that 80% do not require addition ASMs then an additional 10 children will be studied using LVT at this dosage. If it fails to adequately control seizures, the neuroprotective strategy of BCV plus LVT for those in coma a higher dose (150%) will be studied, namely a 60 mg/kg loading dose followed by 45mg/kg every 12 hours given via nasogastric tube for 3 days or until coma resolution. In addition to assessing whether or not the 150% higher LVT dose should be tested, the DMC will also review the accumulating safety data after each adverse event potentially related to the intervention (as defined below) occurs, using a Bayesian continuous monitoring approach for safety. The Bayesian approach uses information from other studies to define a prior distribution for an expected rate of an adverse event before the trial starts, thus formally inferring available knowledge on safety on children with cerebral malaria in these settings. After each child completes 72 hours from enrolment, they will be defined as having had a clinically important adverse event potentially related to the intervention or not. This information is used to iteratively update the prior distribution and to estimate a posterior distribution. The posterior distribution is then used to estimate the probability of the clinically important adverse event rate being higher than a defined threshold and is continually updated throughout the trial. If the probability reaches a specific pre-defined value, then the DMC is prompted to consider stopping the trial. Thus, the decision rule to be used by the DMC to consider stopping the trial is based on a high posterior probability (τ) that the estimated percentage of children with clinically important adverse events is above a threshold R (equivalently: Pr(P
_events_>R | data)>τ). Thus, this way of monitoring uses both available knowledge from previous studies and accruing data from the ongoing trial to inform decisions.

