The clinically important adverse events potentially related to the intervention for a Bayesian monitoring approach to be considered by the DMC in this Phase I trial will be an aspiration or respiration depression event (defined as a sudden decrease in oxygen saturations, and/or de-novo coarse chest crepitations, with evidence of gastric reflux/aspirate in the oropharynx). As the Phase II trial comparing levetiracetam to standard of care (control arm) in Malawi had not been reported when this protocol was designed we used the data posted on Trials.gov for the to inform the anticipated event rates. This reported that there were 3/21 events (15%) in the control arm (Trials.gov: NCT01982812). Thus, this has informed a beta prior distribution of (0.23, 1.32) with mean 0.15 (i.e. 15% children experiencing an event) and variance 0.05. We have defined a stopping threshold of 20%, as a previous case series identified very few aspiration events (<1%) in children with acute respiratory failure using the BCV machine
^
35
^. The posterior probability τ was empirically set at 0.95 for the evaluation of this rule
^
47
^. Thus, according to the derived Bayesian decision rule, enrolment will be stopped if the posterior probability of the number of clinically important adverse events being above the target threshold (20%) is higher than 0.95.

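### Intention-to-treat in a non-randomised safety trial, with a stopping rule counted from enrolment, allows any never-treated child to dilute the safety rates

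*Protocol article*

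**What the plan says.** The Statistical analysis section of the protocol article says "Analyses will follow intention-to-treat" and makes no exception for safety. The Interim reviews section sets the unit of the Bayesian rule: "After each child completes 72 hours from enrolment, they will be defined as having had a clinically important adverse event" or not. No exposure to BCV or levetiracetam is required, and the posterior "is continually updated throughout the trial". The rule's constants are in the same section: "this has informed a beta prior distribution of (0.23, 1.32) with mean 0.15"; "We have defined a stopping threshold of 20" per cent; and "The posterior probability τ was empirically set at 0.95".

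The Trial withdrawal section says that "the clinician remains free to give alternative treatment to that specified in the protocol at any stage", and that such children stay in the study for follow-up and data analysis. Under Trial treatments, children enter three groups of 10 in sequence, without randomisation, and BCV is to run from enrolment. Clinical assessment describes non-compliance as limited and gives no rate.

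**The concern.** Intention-to-treat preserves the balance that randomisation creates. Here there is no randomised contrast, and the main product is an event rate among children given a device and a drug. Taken together, the three statements let a child who was enrolled but never started on either treatment enter the safety denominator. If that child has no event, it counts as a treated child without harm.

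Where treated children have the higher event rate, the error runs in the unsafe direction: aspiration, hypercarbia and hypotension rates are understated, and the stopping rule is slower to fire. In a group of 10, each such child is a tenth of the denominator.

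**Working it through.** **Inputs from Interim reviews.** Prior Beta(0.23, 1.32), threshold R = 0.20, cut-off τ = 0.95. The background rate comes from the external control arm: "This reported that there were 3/21 events (15%) in the control arm". (3/21 is 14.3%; 15% is used below as the plan states it.) N = 30 is from Trial treatments.

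**Assumptions, not in the document.** The share of enrolled children never treated is 10% or 20%, or 1 to 3 children. Their event rate is 0% or 15%. The 0% end fits the requirement that events be potentially related to the intervention. The 15% end fits the purely clinical definition of the event.

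**Step 1: reproduce the stated prior.**
- Mean = a/(a+b) = 0.23/1.55 = 0.148.
- Variance = ab/[(a+b)²(a+b+1)] = (0.23 × 1.32)/(1.55² × 2.55) = 0.0496.
- Both agree with the stated 0.15 and 0.05.

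**Step 2: the boundary.** After x events in n children the posterior is Beta(0.23 + x, 1.32 + n − x). The rule fires at the smallest x with Pr(P > 0.20) > 0.95. The treated-only columns assume that the untreated children had no event.

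| Enrolled | All enrolled | 1 untreated, treated only | 2 untreated, treated only | 3 untreated, treated only |
|---|---|---|---|---|
| 10 | 5 | 5 | 5 | 4 |
| 20 | 8 | 8 | 7 | 7 |
| 30 | 11 | 10 | 10 | 10 |

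The shift is 0 or 1 event. At the end of the trial, 10 events in 29 treated children give 0.954 and the rule fires. The same 10 events in 30 enrolled children give 0.943 and it does not.

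**Step 3: chance of firing by child 30.** This is an exact forward recursion with a look after every child. Each enrolled child is untreated with the stated probability. The treated-only version skips untreated children, and the all-enrolled version counts them.

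| True rate in treated | Untreated share | Treated only | All enrolled, untreated rate 15% | All enrolled, untreated rate 0% |
|---|---|---|---|---|
| 30% | 10% | 0.474 | 0.441 | 0.379 |
| 30% | 20% | 0.440 | 0.379 | 0.264 |
| 40% | 10% | 0.820 | 0.785 | 0.737 |
| 40% | 20% | 0.780 | 0.702 | 0.587 |

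**Step 4: when there is no dilution.** If treated and untreated children both have a 15% rate, the all-enrolled rule fires with probability 0.054 at every untreated share examined.

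**The case against.** The strongest reply is that the document shows no never-treated child. BCV starts at enrolment, ward teams deliver the intervention, and non-compliance is described as limited. Most of Protocol treatment discontinuation concerns children who stop early; they have been exposed and belong in a treated set anyway. Alternative treatment after entry does not mean that trial treatment was never begun. In a descriptive study, intention-to-treat may simply mean reporting all enrolled children by cohort, which suits a feasibility question. The Data Monitoring Committee also reviews serious adverse events in real time, so the rule is not the only safeguard.

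Much of this stands, and it limits the size of the point. A reader might infer that every enrolled child certainly enters the stopping-rule denominator and that dilution will occur. The text does not support that. The rule speaks of children who complete 72 hours. Study procedures says that no data are used once consent is withdrawn, while Protocol treatment discontinuation says that data already collected are kept, including after assent without completed deferred consent.

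A reader might also compare the 0.504 chance of firing with 30 treated children against 0.379 with 10% untreated. That overstates the loss, because no choice of analysis set can restore 30 treated children. The fair comparator is 0.474.

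The objection does not remove the stated rule itself. Intention-to-treat is applied to all analyses, the stopping rule sets no exposure condition, and children given other treatment are kept in the analysis. This is a choice made in the text, not a detail left to an analysis plan.

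**Conclusion.** The point holds as a conditional one. Under the plan as written, any enrolled child who never starts BCV or levetiracetam can dilute the safety rates and make the stopping rule less likely to fire, when the event rate in treated children exceeds that in untreated children. The likely size is modest: for one to three such children, 0 or 1 event on the boundary.

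At a 30% treated rate, the loss in the chance of firing is 0.03 to 0.10 with 10% untreated (0.474 − 0.441 and 0.474 − 0.379). With 20% untreated it is 0.06 to 0.18 (0.440 − 0.379 and 0.440 − 0.264). These figures rest on assumed untreated shares and an assumed event rate of 0% to 15% in untreated children.

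Intention-to-treat should not be blamed for the larger dilution of a levetiracetam signal. That comes from carrying the first 10 children, who get BCV without levetiracetam, in the same posterior. If those 10 had no events, the pooled rule would need 8 events in the first 10 levetiracetam children, against 5 on those children alone. That is a separate matter.

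**What to change.** - In Statistical analysis, limit intention-to-treat to the feasibility and seizure descriptions, with all enrolled children in the denominator. Count non-application of BCV as a feasibility failure.
- For safety endpoints and the rule in Interim reviews, use children in whom BCV was started or at least one levetiracetam dose was given. Report safety by regimen received, and show all-enrolled figures alongside.
- Reconcile Study procedures with Protocol treatment discontinuation on the use of data after consent is withdrawn, since this also fixes the denominator.
- Make sure the start of BCV is recorded. Sampling strategy lists drug use, including anti-seizure medication, but does not mention it.

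The cost is a few sentences and possibly one case record form item. The statistical downside is a slightly smaller safety denominator. No clinical rule changes.

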## Ethics statement

Ethical approval has been obtained from Kenya Scientific and Ethics Review Unit (SERU), Nairobi Kenya on 13
^th^ July 2018 (protocol number RES/7/3/1), Imperial College Research Ethics Committee (ICREC) on 19
^th^ June 2018 (protocol number 18IC4511). The trial was registered on the ISRCTN registry protocol number ISRCTN76942974 on the 5
^th^ February 2019 and on the Pan African Clinical Trials PACTR number PACTR202112749708968 20th December 2021.

## Safety

The study will be performed in patients who may potentially benefit from the treatment.

The trial will be recruiting patients with severe illness and likely a high mortality rate. At the start of the trial, the site will receive appropriate training on the use of the machine and will have 2 dedicated clinicians. The monitors and the BCV has an established safety and acceptability record in a wide range of patient populations, including young children.

## Risks

One potential risk of cerebral malaria is aspiration, where saliva or vomit goes into a child’s throat and makes them start to choke. We will monitor very closely for this as all children with coma routinely have nasogastric tubes (tubes down their noses) and regular suction and this would continue in this study. We do not think that BCV device will increase this risk as it was very small in other studies where it has been used (<1%). The other potential risk is children getting too much carbon dioxide in their blood. This will be monitored very carefully in this study. If indicated, we will optimize the BCV protocol by including the co-use of non-invasive high flow air/oxygen by AIRVO2 via nasal cannulae. Both methods of ventilatory support are widely available, and therefore their inclusion would not affect generalisability.

## Benefits

All patients will be closely monitored so that clinical deteriorations can be identified at the earliest opportunity and appropriate therapy initiated. In general, the high dependency ward at Kilifi County Hospital has considerable experience with this population and this will serve to minimise the risks to the patients and the trial. Prior to the start, the dedicated study teams will undergo detailed training on general management of severe malaria and its complications and receive very detailed training management. Hayek have a demonstration suite in London where one or two of the trial team ([name]) will visit and be fully trained before the start of the clinical trial. We will have a live version of the manual of operations which will provide clear and continuously updated guidelines on how to implement the BCV and what signs of deterioration to look for and how to treat these. We believe this will afford all children enrolled in the trial with a higher quality of care. All routine non-trial medications required by the hospital to treat the child will be made available.

The parents or guardians for the children will be asked to return for a follow up clinic visit at day 28, day 90 and day 180, and thus will be offered continuing care for concurrent illness, including any investigations or blood tests that are clinically indicated.

## Plans for dissemination of the study outcomes

This is a Phase I trial of an emergency intervention where our engagement has been at a scientific rather than public/community level. When the results are available, a summary will provide key trial findings and the next steps. If a larger platform trial arose from this study, we aim to develop a dedicated and informed engagement strategy as part of this future trial.

